### Modified taylor complex figure (MTCF)

The Rey-Osterrieth Complex Figure (ROCF) is commonly used in neuropsychology to assess visuospatial abilities in children and adults. The Taylor Complex Figure (TCF) was developed as an alternate form for the ROCF and has been shown in numerous studies since 1990 to be easier to learn and remember than the ROCF. The Modified Taylor Complex Figure (MTCF) has also been shown in several studies to produce comparable total scores, completion time, and validity coefficients to the ROCF [53].

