**Method:**

This study is a randomized, double-blind controlled clinical trial over a 14-week period. 69 stroke subjects will be enrolled and divided into sham stimulation group, ccPAS low frequency group, and ccPAS high frequency group. All groups will receive conventional rehabilitation. The intervention lasted for two weeks, five times a week. Assessments will be performed before the intervention, at the end of the intervention, and followed up at 6 and 14 weeks. The primary assessment indicator is the ‘Fugl-Meyer Assessment of the Upper Extremity ’, secondary outcomes were ‘The line bisection test’, ‘Modified Taylor Complex Figure’, ‘NIHSS’ and neuroimaging assessments. All adverse events will be recorded.

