### Statistical analysis

#### Behavior statistical analysis

IBM SPSS Statistics 25.0 will be used to analyze the measurement data for each of the three groups at four time points. Measures will be tested for normality, and those meeting the normal distribution will be expressed as mean ± standard deviation (x ± s). Within-group comparisons, post-intervention and two follow-up visits will be compared with baseline (first assessment) using ANOVA with repeated measures data, and then two-by-two comparisons (post-hoc) will be performed to observe differences at each time point if the overall difference was statistically significant. One-way ANOVA will be used for comparison between groups, and further two-by-two comparisons were made. Measures that do not pass the normality test will be expressed as marginal, maximum, and minimum values. Non-normally distributed measures will be compared by Friedman test for a group of own pre-post comparisons and Kruska-Walls H test for between-group comparisons. The level of unity significance will be set at P = 0.05, and P < 0.05 is statistically significant.

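### Within-arm MTCF tests against baseline cannot separate practice, recovery and usual rehabilitation from stimulation, so MTCF conclusions should rest on the between-arm comparison alone

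*Protocol article*

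**What the plan says.** The Study design section of the protocol article lists the MTCF as one of several secondary outcomes, without ranking them. Table 1 marks it at week 0, at the end of the two-week intervention, at week 6 and at the last visit. The abstract says "Assessments will be performed before the intervention, at the end of the intervention, and followed up at 6 and 14 weeks"; Table 1 heads its last column as week 10. On either reading there are four administrations within 14 weeks, the second about two weeks after the first.

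The MTCF section describes three figures. Of the TCF it says "The Taylor Complex Figure (TCF) was developed as an alternate form for the ROCF", and that it proved "easier to learn and remember than the ROCF". Of the instrument actually used, in comparing it with the ROCF, it says "The Modified Taylor Complex Figure (MTCF) has also been shown in several studies to produce comparable total scores, completion time, and validity coefficients to the". Only the MTCF is scheduled, and no rotation of forms is mentioned.

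The Behavior statistical analysis section states: "IBM SPSS Statistics 25.0 will be used to analyze the measurement data for each of the three groups at four time points". Within groups, "Within-group comparisons, post-intervention and two follow-up visits will be compared with baseline (first assessment) using ANOVA with repeated measures data", followed by pairwise comparisons if the overall test is significant. The alternative is that "Non-normally distributed measures will be compared by Friedman test for a group of own pre-post comparisons". Between groups it plans one-way ANOVA or a Kruskal-Wallis test. Significance is P < 0.05 throughout.

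**The concern.** A complex figure is a task on which people may do better the second time because they have seen it before. A within-arm change from baseline contains that practice gain, plus natural recovery, plus the conventional rehabilitation given to every arm, plus any effect of stimulation. The within-arm test asks only whether the sum differs from zero, and nothing in the planned analysis separates the parts.

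At stake is a specific misreading. A report that the MTCF improved significantly from baseline in an active arm invites the conclusion that stimulation improved visuospatial ability, although the same result can arise with no stimulation effect. The within-arm tests are planned as inferential tests with a significance threshold, and the text does not say that conclusions about treatment will be drawn only from the between-arm comparison.

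**Working it through.** **Inputs from the article.** 18 completers per arm, 23 randomised per arm, and two-sided significance at 0.05 in the analysis section. The sample size reproduces: with means 8.11, 6.87 and 17.62, SD 8.83 and alpha 0.025, the noncentral F distribution gives power 0.881 at 17 per arm and 0.902 at 18, so 18 is the minimum, and 18 / 0.8 = 22.5, rounded up to 23. That calculation does not concern the MTCF; it only supplies the two values of n.

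**Inputs assumed.** The article gives neither an MTCF practice gain nor a retest correlation. Let g be the mean practice gain in SDs of the score and r the correlation between two visits, with equal variances and no treatment effect.

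**One paired comparison with baseline.** The SD of the change, in SDs of the score, is sqrt(2(1 − r)). The standardised mean change is dz = g / sqrt(2(1 − r)), and the noncentrality is dz × sqrt(n) on n − 1 degrees of freedom. Worked case, r = 0.7, g = 0.3, n = 23: dz = 0.3 / sqrt(0.6) = 0.387; noncentrality 0.387 × sqrt(23) = 1.857; critical t on 22 df = 2.074; probability of significance 0.43.

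| Practice gain g (SD), r = 0.7 | n = 18 | n = 23 |
|---|---|---|
| 0 | 5% | 5% |
| 0.1 | 8% | 9% |
| 0.2 | 18% | 22% |
| 0.3 | 34% | 43% |
| 0.5 | 73% | 84% |

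Sensitivity to r at n = 23, for gains of 0.2 to 0.5 SD: 18% to 73% at r = 0.6, and 31% to 95% at r = 0.8.

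**The four-visit overall test.** The plan makes pairwise comparisons only after a significant overall repeated-measures ANOVA, so that test was simulated (2,000 runs per setting). The assumptions were a correlation of 0.7 between all visits, a gain of g at the second visit rising to 1.2g and 1.3g at the third and fourth, the same in all arms, and no treatment effect.

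| Gain at second visit (SD) | Sham arm significant, n = 18 | Sham arm significant, n = 23 | Between-arm ANOVA significant, either n |
|---|---|---|---|
| 0 | 5% | 5% | 4% to 6% |
| 0.2 | 22% | 27% | 5% to 6% |
| 0.4 | 74% | 85% | 4% to 5% |
| 0.6 | 98% | 100% | 4% to 5% |

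The last column covers both the last-visit score and the change from baseline. The overall test therefore gives no protection: it responds to the practice gain as the paired test does. The between-arm test stays at its nominal level, because a gain common to all arms drops out of the difference.

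**The case against.** The strongest reply is that randomisation already deals with this. The sham arm has the same MTCF schedule, between-group tests are planned, and the article nowhere says that a within-arm change will be taken as proof of efficacy. The first part stands: a practice gain equal across arms does not bias the between-arm comparison. The reply does not dispose of the within-arm tests, which remain planned at P < 0.05 with nothing to limit how they may be interpreted.

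Several stronger readings are tempting, and the article does not support them:

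- **That the MTCF is the main endpoint for the V1 hypothesis.** It is one unranked secondary outcome beside line bisection. The stated aim is motor recovery, measured by FMA-UE.
- **That the article itself concedes a practice problem with the MTCF.** The remark "easier to learn and remember than the ROCF" is about the TCF; the MTCF is then described as comparable with the ROCF.
- **That one identical drawing is certainly used at every visit.** This is an inference from the MTCF being the only figure scheduled. A condensed article may leave parallel forms, and whether the figure is copied or recalled, to the full protocol.
- **That familiarity pushes scores to a ceiling and shrinks differences between arms.** No MTCF scale, baseline level or maximum is given, so this cannot be assessed.

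It is also fair to say that the size is wholly assumed. At a gain of 0.1 SD the excess over 5% is small.

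**Conclusion.** The point holds for the within-arm MTCF tests only. As planned, they can be significant in any arm, sham included, with no stimulation effect. Under a retest correlation of 0.7 and a practice gain of 0.1 to 0.5 SD, one comparison with baseline is significant about 8% to 73% of the time with 18 per arm, and 9% to 84% with 23, where 5% is nominal. These figures rest on an assumed gain and correlation, and they count practice alone; recovery and conventional rehabilitation would add to the change if they also raise scores.

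A reader might infer that the trial's MTCF result is biased as a whole, or that the primary analysis is compromised. Neither follows: the between-arm contrast is unbiased when practice is equal across arms, and the primary FMA-UE is not affected by this point. This is a matter of how one secondary outcome is interpreted. It should be corrected because the correction is almost free and prevents a misleading claim.

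**What to change.** In the Behavior statistical analysis section, state that any conclusion about a treatment effect on the MTCF will rest only on the between-arm comparison, preferably an analysis of covariance adjusted for the baseline MTCF score. Report within-arm MTCF changes as descriptive summaries, without significance claims.

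The cost is a sentence or two of text. The baseline score is already collected, and the visits, assessors and sample size stay as they are.

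Alternating the MTCF with a comparable form across visits, with the starting form counterbalanced within each arm, is optional and does not replace this change. It would reduce learning of a particular figure but not general familiarity with the task. With two forms over four visits, each form still recurs: the third visit repeats the baseline form, while the second and fourth mix change with any difference between forms. Counterbalancing spreads that difference over the arms at the price of some added noise.

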### National institutes of health stroke scale (NIHSS)

The NIHSS is a 15-item impairment scale, intended to evaluate neurologic outcome and degree of recovery for patients with stroke [54]. The scale assesses level of consciousness, extraocular movements, visual fields, facial muscle function, extremity strength, sensory function, coordination (ataxia), language (aphasia), speech (dysarthria), and hemi-inattention (neglect). The NIHSS was designed to assess differences in interventions in clinical trials.

### Functional magnetic resonance imaging (fMRI)

A 3.0T United Imaging uMR770 MRI system (United Imaging, Shanghai, China) with a standard cranial 32-channel coil will be used. Resting-state fMRI will be acquired using an echo-planar imaging (EPI_BOLD) sequence, with the following scan parameters: TR)/ TE : 3000/30 ms, flip angle (FA): 90°, field of view (FOV) : 220 × 220 mm, matrix size : 64 × 64, slice thickness : 3 mm, slices : 43, and a total of 240 time points were acquired with a scanning time of 12 min.

### Diffusion tensor imaging (DTI)

T1-weighted magnetization-prepared rapid acquisition will be performed with the following parameters: repetition time/inversion time/echo time = 1900/900/2.93 milliseconds, flip angle = 9°, FOV = 256 × 256 mm^2^, section thickness = 1.0 mm sagittal acquisition, acquisition matrix = 256 × 256, and number of averages = 1. Diffusion-weighted images were acquired based on a single shot spin EPI in the axial plane: repetition time/echo time = 10,000/89, flip angle 90, slice thickness 2.0 mm, in-plane resolution 1.875 mm, and 60 noncolinear directions (b = 0, 1000 s/mm^2^).

### Data management

All participants who have provided their informed consent and the results of each assessment will be recorded in both physical and electronic formats. The physical data will be stored by the assessor, who will replace the participants’ real names with their assigned numbers, and create a digital copy of the results for the data analysts. The entire file will be encrypted, and only the data analysts and assessors will have access to it for data verification, to ensure the security and reliability of the data. The Clinical Research Management Center of Yueyang Hospital of Integrated Traditional Chinese and Western Medicine (Shanghai University of Traditional Chinese Medicine) is responsible for supervising the experimental data, which will be stored for three years after the study is completed before being erased.

### Statistical analysis

#### Behavior statistical analysis

IBM SPSS Statistics 25.0 will be used to analyze the measurement data for each of the three groups at four time points. Measures will be tested for normality, and those meeting the normal distribution will be expressed as mean ± standard deviation (x ± s). Within-group comparisons, post-intervention and two follow-up visits will be compared with baseline (first assessment) using ANOVA with repeated measures data, and then two-by-two comparisons (post-hoc) will be performed to observe differences at each time point if the overall difference was statistically significant. One-way ANOVA will be used for comparison between groups, and further two-by-two comparisons were made. Measures that do not pass the normality test will be expressed as marginal, maximum, and minimum values. Non-normally distributed measures will be compared by Friedman test for a group of own pre-post comparisons and Kruska-Walls H test for between-group comparisons. The level of unity significance will be set at P = 0.05, and P < 0.05 is statistically significant.

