## Methods and analysis

### Study design

This study is a double-blind randomized controlled trial, and the protocol is registered with the Chinese Clinical Trials Registry. A total of 69 participants will be divided 1:1:1 into three groups. The control group will receive conventional treatment plus sham ccPAS, the ccPAS low-frequency group received conventional treatment plus 0.2 HZ of ccPAS, and the ccPAS high-frequency group will receive conventional treatment plus 5 HZ of ccPAS.

Each group will receive the intervention five times per week for two weeks. The researcher will follow up with subjects in week six and week fourteen respectively (as shown in Fig. 1 and Table 1).T The primary outcome measure will be the ‘Fugl-Meyer Assessment of the Upper Extremity (FMA-UE)’, secondary outcomes will include ‘The line bisection test’, ‘Modified Taylor Complex Figure (MTCF)’, ‘NIH stroke scale (NIHSS)’, and’ functional Magnetic Resonance Imaging(fMRI)’ as well as ‘Diffusion tensor imaging (DTI)’.

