### Sample size calculation

In this study, the sample size was determined using a multiple group mean comparison method. The sample calculation formula is $$n = {\varphi ^2}\left( {\sum {S_i^2/g} } \right)/\left[ {{{\sum {\left( {{{\bar X}_t} - \bar X} \right)} }^2}/\left( {g - 1} \right)} \right]$$

The number of groups(g) is three, and the number of participants in the control and ccPAS low-frequency groups and the ccPAS high-frequency group was 1:1:1. α is the probability of rejecting a true null hypothesis, α is set to 0.025. β is set to 0.1, power(1-β) is the probability of rejecting a false null hypothesis. K is the group means multiplier; k is 1. The value of φ is obtained by checking the table according to α, β, v1, v2.According to previous studies, the three group means are set to 8.11 6.87 17.62, the within group standard deviation (σ) is 8.83 [43]. Using PASS 15 analysis, we get that the total sample size is 54 and the sample size of each group is 18. Considering the 20% dropout rate, the total sample size of the study should be set to 69 and the sample size of each group is 23.

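### Arms are compared by one-way ANOVA without baseline FMA-UE, and change from baseline is tested only inside each arm; adjusting for baseline costs almost nothing

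*Protocol article*

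**What the plan says.** FMA-UE is the primary outcome (Study design). Table 1 schedules it at baseline, at the end of the two-week intervention and at two follow-ups.

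The Behavior statistical analysis section splits the tests into two sets.

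- Within each arm: "Within-group comparisons, post-intervention and two follow-up visits will be compared with baseline (first assessment) using ANOVA with repeated measures data". If normality fails: "Non-normally distributed measures will be compared by Friedman test for a group of own pre-post comparisons".
- Between arms: "One-way ANOVA will be used for comparison between groups, and further two-by-two comparisons were made", or a Kruskal-Wallis test if normality fails.

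Baseline appears only in the first set. No covariate, change score or group-by-time interaction is named for the second. The section does not say whether the one-way ANOVA is run on the score or on its change, and it labels no test or visit as primary.

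The Sample size calculation section also plans a one-way comparison of three means: "the three group means are set to 8.11 6.87 17.62, the within group standard deviation (σ) is 8.83". It does not say whether these figures are FMA-UE scores or changes in FMA-UE.

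**The concern.** Baseline FMA-UE is collected for every patient, and it will usually predict the later score. A between-arm test that ignores it has two costs.

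- Precision: the part of the outcome variance that baseline explains stays in the error term.
- Chance imbalance: in a comparison of scores, any baseline difference between arms passes into the result in proportion to the correlation. In a comparison of changes, regression to the mean leaves a partial imbalance of the opposite sign.

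The within-arm tests do not fill the gap. All three arms receive conventional rehabilitation, so a change from baseline in an active arm mixes rehabilitation, natural recovery and retest effects with any effect of ccPAS. A significant change in one arm beside a non-significant change in another is not a comparison of the two arms. A reader could nevertheless take it for one.

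**Working it through.** **Inputs from the document.** Means 8.11, 6.87 and 17.62; SD 8.83; three arms at 1:1:1; planning alpha 0.025; power 0.90; 20% dropout (Sample size calculation). Analysis alpha 0.05 (Behavior statistical analysis).

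**Assumed.** The baseline-to-post correlation r of FMA-UE is not given and is taken as 0.3 to 0.9. Baseline and post scores are taken to have equal SD.

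**Step 1: the plan's own figure.** The grand mean is 32.60/3 = 10.87. The deviations are -2.76, -4.00 and 6.75, and their squares sum to 69.18. At n = 18 the noncentrality is 18 × 69.18 / 8.83² = 15.97, with 2 and 51 degrees of freedom. Power at alpha 0.025 is 0.902; n = 17 gives 0.881. So 18 per arm and 54 in total reproduce. Dropout: 18/0.8 = 22.5, hence 23 per arm and 69 in total. The stated N is right for the stated test.

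**Step 2: ANCOVA.** The residual SD is the post-score SD × √(1 − r²), with one error degree of freedom fewer (50). All figures below are for n = 18 per arm and alpha 0.025.

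*Reading A: 8.83 is the SD of the score, and the ANOVA compares scores.*

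| r | ANOVA power | ANCOVA SD | ANCOVA power |
|---|---|---|---|
| 0.3 | 0.90 | 8.42 | 0.93 |
| 0.5 | 0.90 | 7.65 | 0.97 |
| 0.7 | 0.90 | 6.31 | >0.99 |
| 0.9 | 0.90 | 3.85 | >0.99 |

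*Readings B and C: 8.83 is the SD of change.* The post-score SD is then 8.83/√(2(1 − r)), and the ANCOVA SD is 8.83 × √((1 + r)/2). Reading B runs the ANOVA on change; reading C runs it on raw scores.

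| r | B: ANOVA on change | C: raw-score SD | C: ANOVA on raw score | ANCOVA SD | ANCOVA power |
|---|---|---|---|---|---|
| 0.3 | 0.90 | 7.46 | 0.98 | 7.12 | 0.99 |
| 0.5 | 0.90 | 8.83 | 0.90 | 7.65 | 0.97 |
| 0.7 | 0.90 | 11.40 | 0.67 | 8.14 | 0.95 |
| 0.8 | 0.90 | 13.96 | 0.47 | 8.38 | 0.93 |
| 0.9 | 0.90 | 19.74 | 0.23 | 8.61 | 0.92 |

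In every row ANCOVA has more power than the unadjusted test.

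**Step 3: chance imbalance.** The standard error of the baseline difference between two arms is SD × √(2/n). That is 0.33 SD at n = 18 and 0.29 SD at n = 23. For a baseline SD of 8.83 (an illustration), it is 2.9 or 2.6 points. A comparison of raw scores carries r times the realised difference.

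**Step 4: within-arm tests.** Suppose all three arms have the same true gain, so that ccPAS adds nothing, with change SD 8.83, n = 18 and a paired t test at 0.05 in each arm. With p the power in one arm, the chance that at least one active arm is significant while sham is not is (1 − p)(1 − (1 − p)²).

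| True gain in every arm | p | Chance of the misleading pattern |
|---|---|---|
| 3 | 0.27 | 34% |
| 4 | 0.44 | 38% |
| 5 | 0.62 | 33% |
| 6 | 0.78 | 21% |
| 8 | 0.95 | 5% |

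If 8.11 is the gain in sham (an assumption), the sham arm alone reaches significance with probability 0.96.

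**The case against.** **The ANOVA is valid.** Under randomization an unadjusted comparison controls type I error. This stands: the point concerns efficiency and interpretation, not bias.

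**The text does not say score or change.** A reader might infer that no test compares change across arms. The document does not support that as a fact. If the planning figures are gains, the natural reading is that gains are also what the ANOVA compares. Reading B then applies, and ANCOVA adds 2 to 9 points of power over the range of r.

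**A collapse in power is not established.** A reader might infer that power falls to 67%, 47% or 23%. Those figures need a change-score SD, a raw-score ANOVA and r of 0.7 or more, all together. At r = 0.5 there is no loss, and at r = 0.3 power exceeds the plan's. They also use the planning level ("α is set to 0.025"), whereas the analysis section says "The level of unity significance will be set at P = 0.05". At 0.05 the same three cases give 0.77, 0.59 and 0.32 with 18 per arm, and 0.87, 0.71 and 0.41 with all 23.

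**Nothing says efficacy will be judged on the within-arm tests.** This is true; a between-arm test is planned. At a gain near 8 points sham would usually be significant as well, and the misleading pattern has a chance of only 5%. It reaches a third or more only for smaller assumed gains of 3 to 4 points, and about a third at 5.

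**A fuller analysis plan may name covariates.** It may, and silence alone would be no finding. Here, though, the article names the tests and gives baseline a role in one set only.

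**Conclusion.** The concern holds as a precision and interpretation point that should be fixed. As written, the plan uses baseline FMA-UE only inside arms, and the between-arm test has no baseline or group-by-time term. That ANCOVA is more powerful than the planned test does not depend on which reading is right; only the size of the gain does. If the SD of 8.83 belongs to whatever the ANOVA compares, planned power is 0.90 and ANCOVA gives 0.93 to above 0.99 (scores) or 0.92 to 0.99 (changes). If 8.83 is the SD of change but raw scores are compared, power ranges from 0.98 down to 0.23 as r goes from 0.3 to 0.9, against 0.99 down to 0.92 with ANCOVA. These figures rest on an assumed r, equal SDs at baseline and post, n = 18 per arm and alpha 0.025. Neither an invalid between-arm test nor an undersized trial follows from the document.

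**What to change.** In the Behavior statistical analysis section:

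- Make the between-arm FMA-UE analysis an ANCOVA of the post-intervention score on arm, with baseline FMA-UE as covariate. A mixed model with baseline, arm, visit and arm-by-visit would serve equally.
- Report the adjusted differences from sham with confidence intervals.
- Label the within-arm tests descriptive.

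In the Sample size calculation section, state whether the three means and 8.83 are scores or changes.

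The cost is one error degree of freedom and some wording. Baseline is already collected, and the sample of 69 need not grow.
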